**7. Trial design**

This is a phase II/III, randomized, double-blind, placebo-controlled study of the safety and efficacy of chemoprophylactic tenofovir, administered orally once daily to IDUs. The study will be conducted in Bangkok at 17 BMA Drug Treatment Clinics. Study participants will be randomized (1:1) to receive tenofovir 300 mg or placebo. Participants will be evaluated for adverse events and HIV seroconversion.

The primary goals of this study are to assess the safety and efficacy of daily tenofovir to prevent parenteral HIV infection among IDUs. Assessment of changes in HIV associated risk behaviors, adherence to study drug, and, among IDU who become HIV-infected during the trial, evaluation of HIV viral load set point, CD4 counts, genetic characterization of infecting HIV viruses, and antiretroviral resistance will also be done.

**7.1 Primary endpoints**

The primary efficacy endpoint will be measured by:

- Rates of HIV seroconversion measured at monthly intervals

The primary safety endpoints will be measured by:

- The frequency of Grade 3 or 4 renal or hepatic function laboratory toxicities or clinical toxicities in blinded tenofovir and placebo arms, as defined by the Gilead-modified NIAID Adult Common Toxicity Tables, and which cannot be directly attributed to a cause other than study medications
- The frequency of adverse clinical events in tenofovir and placebo arms

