**11.1 Risks**

There are few anticipated health risks to participation in the trial other than minor discomfort associated with physical examinations and blood specimen collection. Some injection and sexual behavior questions may be embarrassing. There have been reports of decreased bone growth and bone strength in studies of tenofovir in animals and reports of renal injury in humans (please, see section 9.1.3).10, 21-23 A small number of persons randomized to tenofovir may experience changes is bone growth or renal function, but most will not and some persons randomized to placebo may also experience these health events. Participants will be monitored closely for clinical or laboratory evidence of bone or renal abnormalities. Based on previous studies, participants randomized to tenofovir may experience gastrointestinal discomfort (e.g., abdominal pain, nausea, vomiting, diarrhea). It is anticipated that prompt discontinuation of study product should quickly resolve any side effects and that no long-term effects should be experienced by the participants.

Among trial participants who become HIV-infected while on tenofovir there is a risk the virus will develop tenofovir resistance. Studies have shown that tenofovir resistance is uncommon, slow to develop, and low level.10 HIV tests will be performed monthly to limit time HIV infected participants will be on tenofovir monotherapy. Based on anticipated enrollment, expected HIV incidence, and trial data,10 it is unlikely any participants will develop tenofovir resistance. HIV infected participants will be tested for tenofovir resistance.

Participants may believe that study drug will protect them from HIV infection and may increase their HIV-related risk behaviors. Potential participants will be told during the informed consent process that we do not know if tenofovir prevents HIV infection and we will not know who is taking tenofovir. Risk reduction counseling will be provided at enrollment and at monthly follow-up visits (please see section 11.4.3). Analysis of data from the AIDSVAX B/E vaccine trial conducted in the same 17 drug treatment clinics showed that participant HIV-related risk behaviors declined by > 30% during the course of the 36 month study.5

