**12.8.2 Management of serum creatinine elevation**

The baseline serum creatinine is defined as the last value obtained from the laboratory prior to the administration of the first dose of study drug.

**All grades:** Continue study medication for up to 3 days whileserum creatinine value is confirmed.

**Confirmed grade 1:** Continue study medication at the discretion of the study physician and monitor as clinically indicated, generally weekly until serum creatinine value is within normal limits (Grade 0).

**Confirmed grade 2-4:** Permanently discontinue study drug and monitor as clinically indicated, generally weekly until serum creatinine value returns to within normal limits (Grade 0).

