**Appendix D. Gilead Modified Common Toxicity Grading Scale – Adults**

IV = intravenous

|  | **Grade 1** | **Grade 2** | **Grade 3** | **Grade 4** |
| --- | --- | --- | --- | --- |
| **SERUM CHEMISTRY** | | | | |
| Creatinine (mg/dL) | An increase   0.5 from baseline | 2.1 – 3.0 | 3.1 – 6.0 | >6.0 |
| BUN (mg/dL) | 30 – 60 | 61 – 120 | 121 –240 | >240 |
| Magnesium (mEq/L) | 1.0 - <1.2 | 0.9 - <1.0 | - | - |
| Phosphorus (mg/dL) | 2.0 – 2.2 | 1.5 – 1.9 | 1.0 – 1.4 | <1.0 |
| Glucose (mg/dL) | 55 – 64 or  116 – 160 | 40 – 54 or  161 – 250 | 30 – 39 or  251 – 500 | <30 or  >500 |
| Bilirubin (mg/dL) | 1.3 – 1.8 | 1.9 – 3.0 | 3.1 – 6.0 | >6.0 |
| Amylase (U/L) | 97 – 131 | 132 – 175 | 176 – 439 | >440 |
| Lipase (U/L) | 154 – 210 | 211 – 279 | 280 – 699 | >699 |
| Creatine Kinase (U/L)  *(unrelated to trauma, exercise, or IM injection)*  Male  Female | 248 – 498  211 – 423 | 499 – 990  424 – 845 | 991 – 1980  846 – 1690 | >1980  >1690 |
| Cholesterol (mg/dL) | >ULN – 300 | 301-400 | 401-500 | >500 |
| Triglycerides (mg/dL) | - | 400 – 750 | 751 – 1200 | >1200 |
| Sodium (mEq/L) | 130 - <131 or  148 – 150 | 123 -129 or  151 – 157 | 116 -122 or  158 – 165 | <116 or  >165 |
| Potassium (mEq/L) | 3.0 – 3.3 or  5.6 – 6.0 | 2.5 – 2.9 or  6.1 – 6.5 | 2.0 – 2.4 or  6.6 – 7.0 | <2.0 or  >7.0 |
| Bicarbonate (mEq/L) | 16 - <17 | 11-15.9 | 8 – 10.9 | <8 |
| Calcium (mg/dL)  *(Ionized)*  Calcium (mg/dL)  *(corrected for albumin)* | 3.0 – 3.4 or  5.6 – 6.0  7.8 - <8.4 or  10.6 – 11.5 | 2.5 – 2.9 or  6.1 – 6.5  7.0 – 7.7 or  11.6 – 12.5 | 2.0 – 2.4 or  6.6 – 7.0  6.1 – 6.9 or  12.6 – 13.5 | <2 or  >7.0  <6.1 or  >13.5 |

|  | **Grade 1** | **Grade 2** | **Grade 3** | **Grade 4** |
| --- | --- | --- | --- | --- |
| **For patients with normal LFTs at baseline (< 2x ULN)** | | | | |
| AST or SGOT (U/L)  *Male*  Female | 45 – 90  43 – 85 | 91 – 180  86 – 170 | 181 – 360  171 – 340 | >360  >340 |
| ALT or SGPT (U/L)  *Male*  *Female* | 54 – 108  43 – 85 | 109 -215  86 – 170 | 216 – 430  171 – 340 | >430  >340 |
| Alkaline Phosphatase (U/L)  *Male 15-20 y*  *Male 21-59 y*  *Female 15-59 y* | 313 – 625  138 – 275  138 – 275 | 626 – 1250  276 – 550  276 – 550 | 1251 – 2500  551 – 1100  551 – 1100 | >2500  >1100  >1100 |
| **HEMATOLOGY** | | | | |
| Hemoglobin (g/dL) | 8.0 – 9.4 | 7.0 – 7.9 | 6.0 – 6.9 | <6.0 |
| Absolute Neutrophil Count (cells/mm3) | 1000 – 1500 | 750 – 999 | 500 – 749 | <500 |

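### Study drug stops permanently at confirmed grade 2 creatinine, but the first primary safety endpoint counts renal laboratory toxicity only from grade 3, so it can under-count creatinine toxicity by an unknown share

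*Protocol*

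**What the plan says.** Section 7.1 lists two primary safety endpoints. The first is "The frequency of Grade 3 or 4 renal or hepatic function laboratory toxicities or clinical toxicities in blinded tenofovir and placebo arms", limited to events "which cannot be directly attributed to a cause other than study medications". The second is "The frequency of adverse clinical events in tenofovir and placebo arms", with no grade threshold.

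Appendix D grades serum creatinine (mg/dL) at grades 2 and 3 as "2.1 – 3.0 | 3.1 – 6.0", with grade 4 above 6.0.

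Section 12.8.2 deals with serum creatinine alone. At any grade the value is confirmed first: "Continue study medication for up to 3 days". For confirmed grade 2 to 4 the instruction is "Permanently discontinue study drug and monitor as clinically indicated, generally weekly until serum creatinine value returns to within normal limits". It carries no condition on attributed cause.

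Section 12.8.1 covers all other laboratory values and clinical events. Drug may continue at grades 1 and 2. Withholding for a possibly drug-related event begins at confirmed grade 3.

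Section 11.1 cites reports of renal injury in humans and adds: "Participants will be monitored closely for clinical or laboratory evidence of bone or renal abnormalities".

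**The concern.** For every laboratory value except creatinine, the grade at which drug is withheld for toxicity is also the grade at which the first primary safety endpoint starts to count. For creatinine the stop comes one grade earlier. Suppose a participant's creatinine rises gradually, is found at 2.1 to 3.0 mg/dL and is confirmed. That participant loses study drug permanently because of renal function, yet contributes nothing to the first endpoint unless creatinine keeps rising after the stop.

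Safety is one of the two primary objectives (section 6.1), and renal injury is one of the few specific risks that the protocol names. If tenofovir raises creatinine, the stop intervenes mainly in the tenofovir arm. The arms could then look alike on the first endpoint while creatinine-related discontinuations differ. Under section 14.2 the interim reports give number, percent and rate for primary and secondary outcomes but only a line listing for adverse events, so the choice of named outcome affects what the DSMB sees as a rate.

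**Working it through.** **Step 1: thresholds side by side**

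| Item | Creatinine | Other laboratory values |
|---|---|---|
| Drug withheld or stopped for toxicity | confirmed grade 2, from 2.1 mg/dL (12.8.2, Appendix D) | confirmed grade 3, if possibly drug-related (12.8.1) |
| First primary safety endpoint begins | grade 3, from 3.1 mg/dL (7.1, Appendix D) | grade 3 (7.1) |
| Gap | one grade | none |

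A creatinine rise counts under the first endpoint in two ways. It may pass from below grade 2 to grade 3 between draws, which are at months 1 and 2 and then every 3 months (Appendix C). Or it may go on rising after the stop.

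**Step 2: the plan's own safety power**

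The protocol states no event rate or power for creatinine. The nearest figure is Table 3 in section 13.1, on SAEs: 1,000 per arm, 7% v 11%, two-sided 0.05, stated power 86%. With a continuity correction,

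Power = Φ[(d − 1/n − 1.96·SE0) / SE1]

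- d = 0.11 − 0.07 = 0.04 and 1/n = 0.001
- SE0 = √(0.09 × 0.91 × 2/1000) = 0.01280
- SE1 = √((0.07 × 0.93 + 0.11 × 0.89)/1000) = 0.01277
- (0.039 − 0.02508)/0.01277 = 1.09, and Φ(1.09) = 0.862

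This reproduces the stated 86%. The other rows also agree (11.6, 34.7, 64.3, 96.3 and 99.3% against 11, 34, 64, 96 and 99%). The sample size and alpha below follow this section.

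**Step 3: illustration for creatinine**

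The rates are assumptions, not protocol figures: confirmed grade 2 or higher in 2.0% on tenofovir and 0.5% on placebo. A share s of these, the same in both arms, goes on to grade 3. Exact power is

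Σi Σj b(i; n, 0.020·s) · b(j; n, 0.005·s) · 1[two-sided Fisher p ≤ 0.05]

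where b is the binomial probability. The row for grade 2 or higher sets s = 1.

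| Events counted | Expected events, 1,000 per arm | Power, 1,000 per arm | Power, 1,200 per arm |
|---|---|---|---|
| Grade 2 or higher | 20 v 5 | 83.6% | 90% |
| Grade 3 or higher, s = 75% | 15 v 3.75 | 70.0% | 79% |
| Grade 3 or higher, s = 50% | 10 v 2.5 | 47.5% | 58% |
| Grade 3 or higher, s = 25% | 5 v 1.25 | 16.5% | 23% |
| Grade 3 or higher, s = 10% | 2 v 0.5 | 1.0% | 2% |

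The 1,200 column is half of the planned 2,400 enrolment. Power falls at every s below 1. How far it falls depends entirely on s, which the protocol does not give. These are powers of a creatinine-only comparison. They are not powers of the first endpoint, which pools renal, hepatic and clinical toxicities.

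**Step 4: is renal discontinuation one defined event?**

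By the Cockcroft-Gault formula in section 8.2, a man aged 30 weighing 60 kg with creatinine 2.1 mg/dL has clearance (140 − 30) × 60 / (72 × 2.1) = 6600/151.2 = 43.7 mL/min. Section 12.8.3 gives a longer dosing interval at 30 to 49 mL/min, whereas section 12.8.2 stops drug permanently at that creatinine once confirmed. Section 8.5 gives grade 4 creatinine, or grade 3 with recurrence, as examples of reasons for withdrawal. The three sections do not define one event.

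**The case against.** The strongest reply is that nothing is lost. Section 12.2 makes an abnormal laboratory finding an adverse event. Section 13.8 compares adverse events, SAEs and abnormal laboratory results between arms, organised by severity and relationship, and includes time-to-event methods. Analysis is by intention to treat, and section 12.8.2 continues creatinine monitoring after the stop. Other renal tests, such as BUN and phosphorus, fall under section 12.8.1 and can reach grade 3 or 4 on drug. Counting severe toxicity under monitored use is also a legitimate primary safety measure.

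Most of this stands. A grade 2 imbalance would be in the database and in a planned general comparison. It does not close the gap in section 7.1. Intention to treat keeps a participant in the assigned arm but does not turn a grade 2 stop into a grade 3 event. The second primary endpoint concerns clinical events, and the protocol elsewhere separates these from laboratory toxicity (sections 12.7.2 and 12.8.1), so a symptom-free creatinine rise does not clearly belong there. SAE reporting does not fill the gap either: section 12.5 makes grade 4 events SAEs and grade 3 events case by case, and does not name grade 2.

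A reader might infer that the stopping rule removes most drug-related renal toxicity from view. The documents do not support that. They give no progression rate, the early stop covers serum creatinine only, and grade 2 events remain recorded and compared. Nor does a null result on grade 3 to 4 counts by itself trigger post-trial provision: section 11.3 ties that to tenofovir being found safe and effective.

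**Conclusion.** The mismatch is real and can be read directly from sections 7.1 and 12.8.2 and Appendix D. For serum creatinine, the event that permanently ends treatment lies one grade below the event that the first primary safety endpoint counts. That endpoint can therefore under-count drug-related creatinine toxicity, and no primary safety endpoint names the grade 2 events.

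The size is unknown. Under the assumed 2.0% v 0.5%, with 1,000 per arm, power for creatinine falls from 83.6% to between 70.0% and 1.0% as the assumed progression share falls from 75% to 10%. Both the rates and the share are assumptions. With chemistries 3-monthly after the early visits, a high share cannot be excluded, and the loss would then be modest. This is an inexpensive improvement to an endpoint definition and does not show that the trial would miss renal harm.

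**What to change.** In section 7.1, add to the primary safety endpoints a between-arm comparison of participants with confirmed grade 2 or higher serum creatinine or permanent discontinuation of study drug for renal function, counted regardless of attributed cause. Keep grade 3 to 4 as a reported subset. Use the same definition in the DSMB tables, with number, percent and rate by arm.

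Reconcile sections 8.5, 12.8.2 and 12.8.3, which give different renal actions, so that renal discontinuation is one unambiguous event. Which clinical rule should apply is not a matter for this review, and none is proposed.

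The endpoint change costs wording in section 7.1 and one table definition. Creatinine is already measured at the scheduled chemistries, and section 12.6 already requires decisions to suspend study drug to be documented. The small downside is that the added comparison includes milder events than grade 3 to 4.

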**7.2 Secondary endpoints**

Changes in HIV associated risk behaviors will be measured by:

- Rates of reported injection drug use and injection drug use frequency during the trial
- Rates of reported needle sharing
- The number of unprotected sexual acts over the course of the trial
- Number of reported sexual partners over the course of the trial
- Proportional use of condoms during sexual intercourse

Medication adherence will be measured as:

- Rates, by interview and documentation on tenofovir adherence card, of participants taking at least six (86%) of seven daily doses of study drug each of the four weeks preceding the monthly study visit

Differences in virologic and immunologic responses to HIV infection among tenofovir and placebo recipients will be measured by:

- Plasma viral load, measured by quantitative RNA PCR, a predictor of clinical progression of HIV disease;14 CD4 cell counts will be measured by flow cytometry
- Rates and nature of HIV antiretroviral genotypic and phenotypic resistance will be measured
- Genetic characteristics of infecting HIV viruses including DNA sequence analysis and antibody binding studies will be conducted

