**9.6 Study drug interruption**

The study drug may be temporarily interrupted if the participant runs out of study drug because of a missed visit or the physician stops study drug to allow resolution of a transient adverse event. In such cases, an HIV test will be done to confirm the participant is HIV-uninfected before the participant resumes study drug.

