**12.8.1 Management of laboratory abnormality *(except serum creatinine elevation)* or clinical event**

**Grade 1 or 2:** Continue study medication at the discretion of the study physician.

**Grade 3 or 4:** May continue study medication, at the discretion of the study physician, for up to 3 days while values are confirmed.

**Confirmed grade 3:** If unrelated to study drug by above definitions, may continue dosing. If causal relationship to study drug possible by above definitions, withhold drug until toxicity returns to < grade 3 then retest to confirm participant is HIV negative then restart study drug. If toxicity > grade 3 recurs, permanently discontinue dosing and follow at scheduled study visits until toxicity resolves.

**Confirmed grade 4:** If unrelated to study drug by above definitions, may continue dosing. If causal relationship to study drug possible by above definitions, permanently discontinue study drug and follow at scheduled study visits until toxicity resolves. Do not rechallenge.

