**12.8.3 Management of creatinine clearance results**

Study medication will be adjusted according to modified Tenofovir dose adjustment for renal impairment guidelines (Gilead Sciences).10

|  | Creatinine Clearance | | |
| --- | --- | --- | --- |
|  | ≥50 mL/min | 30–49 mL/min | < 29 mL/min |
| Recommended Dosing Interval | Every 24 hours | Every 48 hours | Stop study medication |

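### The six-of-seven-daily-doses adherence rule scores a fully compliant participant on the protocol's 48-hour interval as non-adherent, and does the same for most directed holds of two days or more

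*Protocol*

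**What the plan says.** Protocol section 7.2 lists medication adherence as a secondary endpoint. It is measured, by interview and adherence card, as the rate of participants "taking at least six (86%) of seven daily doses of study drug each of the four weeks preceding the monthly study visit". The rule has one form, for all participants.

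Other sections direct some participants to take fewer doses than one a day:

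- Section 12.8.3: "Study medication will be adjusted according to modified Tenofovir dose adjustment for renal impairment guidelines". Its table sets 24 hours at a creatinine clearance of 50 mL/min or more, 48 hours at 30–49 mL/min, and a stop below that.
- Section 12.8.1, for a confirmed grade 3 event possibly related to study drug: "withhold drug until toxicity returns to < grade 3 then retest to confirm participant is HIV negative then restart study drug". No length of hold is given.
- Section 9.6 allows a temporary interruption for two reasons. One is that the participant runs out of drug after a missed visit. The other is that "the physician stops study drug to allow resolution of a transient adverse event".
- Section 12.8.2, for confirmed grade 2–4 serum creatinine: "Permanently discontinue study drug and monitor as clinically indicated, generally weekly until serum creatinine value returns to within normal limits".

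Neither section 7.2 nor section 9.5 (adherence monitoring) says how a changed interval or a directed off-drug period enters the adherence denominator. Section 14.2 asks for interim reports that give medication adherence by arm, and for efficacy analyses that adjust for adherence.

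**The concern.** Section 7.2 states a rule; it does not leave the definition for later. That rule conflicts with section 12.8.3. A participant who follows the renal dosing table exactly cannot reach six doses in any full week on the 48-hour interval, so following the protocol is recorded as failing to adhere. A directed hold can have the same result for the visit windows in which it falls.

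The error need not be balanced between arms. Renal injury is a named risk (section 11.1), and renal laboratory toxicity is part of a primary safety endpoint (section 7.1). If interval changes or toxicity holds are more frequent in one arm, that arm's adherence will look lower for a reason unrelated to participants' behaviour. If the section 7.2 definition is the one used for the adherence-adjusted analyses in section 14.2, the misclassification would carry into what the DSMB sees.

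**Working it through.** **Inputs.** Threshold: six of seven doses in each of four weeks (section 7.2). Visits every 4 weeks, so a 28-day window (section 10.3.2). Interval of 48 hours at clearance 30–49 mL/min (section 12.8.3). Clearance formula: section 8.2. Creatinine grades: Appendix D.

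**The plan's own figure.** 6/7 = 0.857, which rounds to the stated 86%.

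**48-hour interval, every directed dose taken.** Depending on the starting day, the four weeks hold 4, 3, 4, 3 or 3, 4, 3, 4 doses. The weekly share is 3/7 = 43% or 4/7 = 57%. The total is 14/28 = 50%. No full week reaches six.

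**Switch to 48 hours part-way through a window.** From day 26, the last week has doses on days 22–26 and 28, which is 6 of 7 and passes. From day 25, it has days 22–25 and 27, which is 5 of 7 and fails. Only a switch on days 26–28 still passes.

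**Directed hold wholly inside one window, all other doses taken.** A window passes only if no week loses more than one dose.

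- 1 day: passes for 28 of 28 start days.
- 2 days: passes only when split across two weeks (starting on day 7, 14 or 21), so 3 of 27 start days; 24 of 27 fail.
- 3 days or more: at least one week loses two doses or more, so none pass (0 of 26 start days at 3 days, and none at 4 to 8 days).

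A longer hold that crosses a visit date does not fail a window that catches only one of its days. Later windows are unaffected.

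**Can the 48-hour band be reached before the creatinine rule stops drug?** For men, clearance = (140 − age) × weight / (72 × creatinine). Body weights here, and the age in the first example, are assumptions.

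- Man of 45 years, 50 kg, creatinine 1.0 mg/dL: 95 × 50 / 72 = 66 mL/min, above the 60 mL/min cited for entry. At 1.4 mg/dL: 4750 / 100.8 = 47 mL/min, inside the band. The rise of 0.4 is below the 0.5 used for grade 1, and 1.4 is below the grade 2 floor of 2.1.
- Man of 26 years (the median age at screening for the vaccine trial, section 5.1), 60 kg: clearance reaches 50 mL/min at 114 × 60 / (72 × 50) = 1.9 mg/dL, also below grade 2.

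So the band can be entered without a grade 2 stop.

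**Size.** The protocol gives no count of affected participants. Understatement in an arm = share of participant-months affected × share of those that would otherwise be adherent. If one arm had 1–3% more affected participant-months (an assumption) and all would otherwise have been adherent, its rate would fall by 1–3 percentage points relative to the other. The second condition makes this an upper bound for that assumed share.

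**With directed doses as the denominator.** Full compliance on 48 hours scores 14/14 = 100%. The same level over four weeks is 12/14 = 85.7%. Week by week it does not carry over: 3/4 = 75% and 2/3 = 67% both fall short, so no dose could be missed, while a daily participant may miss one each week.

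**The case against.** The strongest reply is that the endpoint may be meant to describe daily drug-taking. The objective in section 6.2 refers to daily tenofovir or placebo, and section 9.5 wants adherence so that safety and efficacy can be read against actual use. On that view, someone on alternate days or off drug did not have daily coverage, and the score is right. This has force, but section 7.2 labels the measure medication adherence and nowhere says coverage is intended. Reporting directed off-drug and altered-interval time separately serves both purposes.

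A statistical analysis plan, not available here, may settle the denominator. That would be a sufficient answer for a gap, but section 7.2 already states a rule that misclassifies.

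Several stronger readings are tempting, and the protocol does not support them:

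- **No participant on a hold can meet the rule.** One-day holds pass, and so do 2-day holds split across two weeks. Because the protocol gives no hold length, it is only plausible, not stated, that waiting for recovery and an HIV retest takes longer.
- **Every interruption under section 9.6 is misclassified.** Running out of drug after a missed visit is genuine non-adherence and is scored correctly.
- **Adherence will be understated on tenofovir.** Nothing in the protocol establishes an excess of affected time on tenofovir. Table 1 in section 9.1.3 shows permanent discontinuation for clinical events at 2% on placebo and 3% on tenofovir, and for laboratory events at 2% and 0.
- **The DSMB's adjusted analyses will be distorted.** Section 14.2 does not say which adherence measure is used, and section 9.5 lists interview, pill count, diary and blood levels.

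**Conclusion.** The point stands as a minor but definite inconsistency in one secondary endpoint. For the 48-hour interval it is exact: full compliance gives 3–4 of 7 doses and is scored non-adherent in every full week. For directed holds it is partial: holds of 3 days or more inside a window, and 24 of 27 placements of a 2-day hold, fail that window only.

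The number affected is unknown and probably small, given the 60 mL/min cited for entry and the permanent stop at confirmed grade 2–4 creatinine. A difference between arms, and any effect on the adherence-adjusted interim analyses, are possibilities. They depend on renal changes or holds differing by arm and on this definition being used there. The primary efficacy analysis, which is by intention to treat (section 13.9), is not touched.

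**What to change.** Reconcile sections 7.2, 9.6, 12.8.1, 12.8.2 and 12.8.3 by stating the denominator:

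- Define adherence as taking at least 6/7 of the doses directed for that participant. Write the level as 6/7, because 12/14 is exactly 6/7 but slightly under 0.86.
- Keep the six-of-seven weekly rule while dosing is daily. Where the interval was altered, apply the level over the whole four-week window (12 of 14 for a full window), not week by week. A week shortened by a hold has the same coarseness (4 of 5 is 80%), so the sponsor may wish to treat it the same way.
- Leave protocol- or physician-directed holds and stops out of the denominator. Continue to count running out of drug after a missed visit as missed doses.
- Tabulate directed off-drug time and altered-interval time separately by arm, so that daily drug coverage can still be read.
- State in section 14.2 whether this is the measure used for adherence adjustment.

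The cost is a few sentences and a little data handling. Section 12.6 has suspension decisions for adverse events documented, but the protocol does not expressly say that interval changes are recorded for scoring, so they would need to be captured. No dosing, hold or stopping rule changes, and no view is taken on any of them.
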